To our knowledge, the field of sleep medicine is without a fully powered, sham-controlled, masked, randomized controlled trial establishing feasibility, acceptability and efficacy of MBLT to improve sleep quality in Veterans with mTBI. Furthermore, to our knowledge, a fully remote randomized controlled trial device intervention protocol has not yet been successfully implemented in Veterans with mTBI–a challenging population not only due to significant participant disability/burden, but also due to the logistical and regulatory challenges of device management and electronic data capture behind the Veterans Affairs (VA) firewall. We sought to fill both gaps by implementing LION (Light vs Ion therapy), whose protocol is described herein. This trial proposed to acquire complete data in n = 120 Veterans allocated 2:1, active-intervention (MBLT, n = 80) versus sham-intervention (deactivated ion therapy, n = 40). MBLT delivered white light (10,000 lux at the eye), whereas the negative ion generator was fully deactivated, but modified to appear “on”, i.e., via installation of a small fan to generate a quiet, whirring sound, as well as a small LED status light. This sham-intervention was modeled from prior work by Lam et al., [28] in which bright light or sham-intervention therapy was compared to fluoxetine for the treatment of depression. Participants in both groups engaged with devices to the same extent (i.e., over 60 minutes within 2 hours after waking) throughout the 28-day intervention period, with the same degree of expectancy and study team interaction. The brand of the light box was chosen due to being commercially available, in use for decades (including within the VA), and previously validated for illuminance metrics and spectral power density [25]. Dose, timing, and duration were all established from prior work investigating the effect of MBLT for the treatment of insomnia, circadian entrainment, and seasonal affective disorder [46–48].

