**Fig 1 pone.0305305.g001:**
[figure not shown]
SPIRT outcomes across time. The Standard Protocol Items: Recommendations for Interventional Trials (SPIRIT) timeline for LION.

The total target sample size of n = 120 participants is based on a priori power analyses considering mean insomnia severity index score as the primary outcome (see below). Using a two-sided students t-test design comparing MBLT to sham (pre- to post-intervention), the minimal detectable clinically relevant between-group difference was set at 7% with a standard deviation of 12% within MBLT and 7.3% within sham groups. This approach achieves β = 0.15 with α = 0.05 (i.e., 85% power; 15% probability of incorrectly accepting the null hypothesis) [49,50].

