### Statistical analyses

The statistical analysis plan was designed to be carried out using GraphPad Prism v9 or R, with alpha defined *a priori* at 0.05, using a thorough descriptive analysis of participant baseline characteristics prior to evaluation of outcomes. Categorical variables will be described using frequencies and percentages. Histograms and boxplots will be used to assess the distribution of continuous variables. Continuous variables that follow an approximately normal distribution will be summarized using means and standard deviations; skewed continuous variables will be reported as medians and interquartile ranges. Potential covariates will also be summarized with descriptive statistics and graphs. As part of our descriptive analyses, we will compare participants who complete versus drop out of the study by baseline characteristics and study arm to ascertain potential biases that may impact this and future studies. Effect size estimates will be reported as Cohen’s d (small = 0.2; medium = 0.5; large = 0.8) or standardized regression coefficients (β) (small = 0.14; medium = 0.39; large = 0.59). We will also report the number needed to treat (NNT) approximated using methods described by Kraemer and Kupfer [71]. The Benjamini-Hochberg procedure will be used to control the false discovery rate for primary outcomes. Statistical outliers will be identified using regression diagnostics to estimate Cook’s Distance, and then a cutoff of 4/n (n = number of participants) will be used to identify outliers. Outliers will be examined for data entry errors, but otherwise retained in analyses. If data violate parametric assumptions via Shapiro-Wilk test, test statistics will be derived using robust standard errors. We will use the intent-to-treat principle and include all participants randomized to treatment irrespective of treatment compliance.

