We will examine patterns of missingness in outcomes over time. Every effort will be made to minimize the risk of systematic missing data. Sensitivity analyses will be performed to assess the influence of missingness and attribute this to either "Random" or "System" causes (appreciating that data are rarely missing completely at random). These analyses will inform the robustness of our findings and potentially obtain better estimates of the magnitude of effects to inform future trials. We will follow the recommendations by Jakobsen et al.[72] to handle missing data for our assessment: (1) <5% without evidence of differential patterns of missingness we will consider this negligible and impute the “best” and “worst” case scenarios for missing data to estimate plausible ranges of MBLT and placebo effects. (2) 5–25% we cue implementation of Markov Chain Monte Carlo (MCMC) multiple imputation to impute missing values and analyze 5 combined imputed datasets. (3) >25% (unlikely) we will not attempt to impute missing values. In the case of (3), the results of the complete case analyses will be reported along with reasons for missingness. In all cases, we will discuss and report the extent of missingness with a clear discussion of study limitations.

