**Primary Sleep Outcome**				
Insomnia severity index				
Pre-intervention	47 (100%)	22 (100%)	24 (100%)	11 (100%)
Post-intervention	43 (91%)	17 (77%)	21 (88%)	10 (91%)

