**Fig 5 pone.0305305.g005:**
[figure not shown]
Intervention adherence. Device use (self-report and objective), sleep diary and actigraphy data collected during intervention (over 28 days) in the active (**A**) and sham (**B**) conditions. The dashed line indicates the 70% threshold for adherence (20 days). Each data point represents a single participant and corresponds to the number of days they have complete data.

With respect to our primary outcome (ISI score), >95% of participants in both study arms have provided both pre- and post-intervention data. Supplemental sleep related outcomes included wrist-based actigraphy and sleep diary entries, the completeness for both of which was expressed in terms of the number of days with full/usable data (i.e., out of a maximum of 14 days for the baseline period and out of a maximum of 28 days for the intervention period). For both actigraphy and sleep diaries, we reported >83% of participants have complete data, defined as a minimum of 10 days of data recorded at baseline (Fig 4A and 4B) and 20 days of data recorded during the intervention period (Fig 5A and 5B), reflecting >70% of days for both periods.

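### Five imputations are too few for a stable p-value if ISI missingness is 12.5%, as Table 3 implies; whether this touches the efficacy verdict depends on which analysis is decisive, which the article leaves open

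*Protocol article*

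**What the plan says.** The Statistical analyses section sets three rules by the extent of missing data:

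- Below 5%, with no differential pattern: missingness is treated as negligible and best-case and worst-case values are imputed.
- From 5% to 25%: Markov Chain Monte Carlo "multiple imputation to impute missing values and analyze 5 combined imputed datasets".
- Above 25%: no imputation; complete cases are reported.

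The same section makes a mixed effects model the analysis of treatment effect over time for each outcome, partly because it can use incomplete records under missing at random. It sets the threshold "with alpha defined *a priori* at 0.05". The imputation rules follow a sentence announcing sensitivity analyses. The article does not say whether the mixed-model result or the imputed result decides efficacy.

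The article describes the completeness of the primary outcome in incompatible ways. Table 3 lists post-intervention ISI for 43, 17, 21 and 10 participants out of 47, 22, 24 and 11. The text below Fig 5 says that ">95% of participants in both study arms have provided both pre- and post-intervention data". The text below Table 3 says that complete pre- and post-intervention data are recorded in 104 participants.

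**The concern.** The number of imputations is stated in the article, so this is not a detail left to a fuller plan. With five, the pooled estimate and its standard error carry Monte Carlo noise. If the result lies near 0.05, a second analyst with the same data and the same plan could reach the other side of the threshold by drawing different random numbers.

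At stake is the repeatability of either the efficacy result or the missing-data sensitivity analysis, depending on the role given to the imputed analysis. Loss of power is not the issue.

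**Working it through.** **1. Which rule applies.** From Table 3: 43 + 17 + 21 + 10 = 91 of 104 observed, so 13/104 = 12.5% missing. By arm: MBLT 9/69 = 13.0%, sham 4/35 = 11.4%. If these 13 stay missing and everyone else up to 120 provides an ISI, the rate is 13/120 = 10.8%, still in the 5–25% band. The other two statements give different answers: more than 95% complete means under 5% missing (the first rule), and 104 complete means none missing.

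**2. The plan's own figure.** Inputs, from the sample-size text below Fig 1 and the Introduction: "Using a two-sided students t-test design comparing MBLT to sham (pre- to post-intervention"); "difference was set at 7% with a standard deviation of 12% within MBLT and 7.3% within sham groups"; 80 v 40; "This approach achieves β = 0.15 with α = 0.05".

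- SD 12 in both arms: SE = 12 × √(1/80 + 1/40) = 2.324; 7/2.324 = 3.012; power ≈ Φ(3.012 − 1.96) = 85.4%. The stated 85% is reproduced.
- SDs as stated: SE = √(144/80 + 53.29/40) = 1.770; 7/1.770 = 3.955; power ≈ Φ(3.955 − 1.96) = 97.7%.

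So on the stated SDs, results near 0.05 are uncommon if the true difference is 7%. They are common at a true difference of 3.5% (3.5/1.770 = 1.98, almost on the threshold).

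**3. Precision lost with m = 5.** Relative efficiency = 1/(1 + FMI/m), where FMI is the fraction of missing information. With FMI ≈ 0.125: 1/(1 + 0.025) = 97.6%. The loss is small.

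**4. Repeatability, by approximation.** The Monte Carlo SD of the pooled z is about s = √(FMI/m): √(0.125/5) = 0.158 at m = 5 and √(0.125/50) = 0.050 at m = 50. If the result with unlimited imputations lies d = |z − 1.96| from the threshold, two runs disagree with probability 2Φ(d/s)[1 − Φ(d/s)].

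| p with unlimited m | d | m = 5 | m = 50 |
|---|---|---|---|
| 0.02 | 0.366 | 2% | 0% |
| 0.03 | 0.210 | 17% | 0% |
| 0.04 | 0.094 | 40% | 6% |
| 0.05 | 0 | 50% | 50% |

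Averaged over p from 0.02 to 0.10, this gives 26% at m = 5 and about 8% at m = 50.

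**5. Repeatability, by simulation.** Set-up: 80/40, SDs 12% and 7.3%, 12.5% of post-intervention ISI missing, imputation from baseline, Rubin's rules with small-sample degrees of freedom, each data set imputed twice independently. The share of all trials in which the two runs disagree at 0.05:

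| True difference | m = 5 | m = 50 |
|---|---|---|
| 3.5% | 9.6% | 2.4% |
| 5.3% | 8.5% | 2.0% |
| 7% (planned) | 2.6% | 0.7% |

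A repeat gave about 0.7–10% at m = 5 and 0.2–3% at m = 50. Where the first p lies between 0.02 and 0.10, 26–32% disagree at m = 5 and about 9% at m = 50.

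A separately coded simulation, with pre–post correlation assumed at 0.3, 0.5 and 0.7 and the band defined on the unlimited-imputation p, gave 31–32% at m = 5, 15–16% at m = 20, 9–10% at m = 50 and 6–7% at m = 100. The rate at m = 5 depends on the band: 46–51% for p 0.04–0.06 and 24–26% for p 0.01–0.10.

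**6. Auxiliary data.** Adding a variable that correlates 0.5–0.7 (assumed) with the ISI change residual gave variance ratios of 0.974 and 0.935, a gain of about 3–6%.

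**The case against.** A reader might infer that the trial's primary p-value would not be reproducible, and that 3 in 10 borderline efficacy results would change on a re-run. The documents do not support that reading, for three reasons.

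- **Role of the imputation.** The named efficacy analysis is a mixed model that needs no imputed ISI, and the imputation rules come in a paragraph about sensitivity and robustness. Nothing says that the imputed result decides efficacy. This objection stands, and it makes the consequence conditional.
- **The 12.5% is contested and interim.** Two statements in the article conflict with Table 3, and the final rate will select the rule. This stands as a need to reconcile. Table 3 gives actual counts, though, and the abstract's figure of under 15% incomplete data fits them.
- **Borderline is not defined in the documents.** Three in ten belongs to a chosen window of p. At the planned difference under 3% of all simulated trials disagree, and even 50 imputations leave about 8–10% disagreement in that window. This stands.

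The simulation also simplifies the plan. It uses baseline only, although ISI at follow-up could lower the missing information, and it tests a plain 0.05 although the plan applies Benjamini-Hochberg to primary outcomes. The figures are therefore indicative.

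It is also tempting to say that the plan ignores sleep data already in hand. That goes too far. The imputation model and the seed are details that an article may leave to the full plan. Table 3 gives group averages of diary and actigraphy days, not availability for the 13 people without ISI. The full questionnaire battery is also complete for only 43 + 17 + 20 + 11 = 91, so the Epworth scale and FOSQ-10 are probably often missing along with ISI.

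None of this defends the number five. A recorded seed would make one run repeatable but would not remove its dependence on the draw; more imputations reduce that dependence.

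**Conclusion.** The point holds in bounded form. The article fixes five imputations for a band that, by Table 3, contains the primary outcome. Near 0.05 that leaves the conclusion partly to the random draw: about 30% disagreement between runs for p 0.02–0.10, against about 8–10% with 50 imputations. Over all simulated trials the rates are about 1–10% against 0.2–3%, and disagreement is rare at the planned difference.

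This rests on Table 3's counts being right, data missing completely at random in the simulation, imputation from baseline, the assumed pre–post correlations and the chosen p window. If the imputed analysis is decisive, the efficacy verdict is exposed. If the mixed model is decisive, the harm is an unstable sensitivity analysis.

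**What to change.** In the 5–25% rule:

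1. Replace five imputed datasets with at least 50, with a recorded seed.
2. Impute within arm, because the sample-size text itself expects SDs of 12% and 7.3%.
3. State whether the mixed model or the imputed analysis is primary for ISI.
4. Reconcile Table 3 with the text below Fig 5 and below Table 3, so that it is clear which missing-data rule applies.

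Optionally, add intervention-period diary and actigraphy summaries as auxiliary variables where they exist, for a modest gain.

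The cost is a few lines of wording and a few minutes of computing, with no new data and no loss of power. The Results section says that formal outcome analyses have not yet been run, so on that account the change can be made without knowledge of results.

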## Results

Formal statistical analyses across participant groups (Tables 1 and 2) or in primary/secondary outcomes have not yet been explored given the ongoing/incomplete status of this randomized controlled trial. However, a central goal of presenting this study protocol was to evaluate overall feasibility and acceptability. This was best demonstrated through evaluating overall participant retention (feasibility; Fig 3) and a combination of protocol fidelity adherence and “data completeness” for primary outcomes (acceptability; Table 3).

**Table 3 pone.0305305.t003:** Feasibility and acceptability.

	MBLT (*n* = 69)		Sham (*n* = 35)	
	mTBI (*n* = 47)	No TBI (*n* = 22)	mTBI (*n* = 24)	No TBI (*n* = 11)
**Device Adherence**				
Self-reported use, *days*	22.8 ± 7.7 (82%)	24.6 ± 6.4 (88%)	22.1 ± 8.5 (79%)	23.5 ± 6.5 (84%)
Objective estimate, *days*	22.4 ± 7.7 (80%)	22.4 ± 8.2 (80%)	-	-
**Primary Sleep Outcome**				
Insomnia severity index				
Pre-intervention	47 (100%)	22 (100%)	24 (100%)	11 (100%)
Post-intervention	43 (91%)	17 (77%)	21 (88%)	10 (91%)
**Additional Sleep Outcomes**				
Actigraphy				
Pre-intervention, *days*	12.4 ± 3.5 (89%)	12.3 ± 0.2 (88%)	11.2 ± 3.3 (80%)	13.5 ± 5.4 (97%)
Post-intervention, *days*	23.5 ± 7.8 (84%)	25.6 ± 6.2 (91%)	24.9 ± 8.2 (89%)	23.8 ± 6.9 (85%)
Sleep Diary				
Pre-intervention, *days*	13.0 ± 3.4 (93%)	14.0 ± 3.4 (100%)	13.0 ± 4.9 (93%)	11.0 ± 0.5 (79%)
Post-intervention, *days*	24.9 ± 8.3 (89%)	25.5 ± 6.4 (91%)	24.8 ± 8.2 (89%)	25.0 ± 6.2 (89%)
**Secondary Outcomes**				
Full questionnaire battery				
Pre-intervention	47 (100%)	22 (100%)	24 (100%)	11 (100%)
Post-intervention	43 (91%)	17 (77%)	20 (83%)	11 (100%)
Cognitive Assessment				
Pre-intervention	47 (100%)	22 (100%)	24 (100%)	11 (100%)
Post-intervention	45 (96%)	22 (100%)	23 (96%)	11 (100%)
DLMO				
Pre-intervention	40 (85%)	18 (82%)	21 (88%)	10 (91%)
Post-intervention	38 (81%)	19 (86%)	20 (83%)	11 (100%)
Biospecimen sample				
Pre-intervention	41 (87%)	19 (86%)	21 (88%)	9 (82%)
Post-intervention	40 (85%)	17 (77%)	20 (83%)	6 (55%)

Data are presented as mean ± standard deviation, or *n* (%). Pre-intervention assessments span a maximum of 14 days. Post-intervention assessments and device adherence spans a maximum of 28 days. DLMO, dim light melatonin onset.

With respect to participant retention, of the *n* = 140 participants who have provided informed consent, *n* = 24 have withdrawn or been terminated (Fig 3), and therefore *n* = 116 (83%) have been retained. At the time of this interim analysis, complete pre- and post-intervention data has been recorded in n = 104 participants and therefore the remaining n = 12 participants have been randomized/allocated and are currently ongoing.

In establishing protocol acceptability, we first considered the rate of missing data and other errors present in major outcome assessments, within the 14-day baseline period. This was examined via participant response rates for sleep diary entries and actigraphy usage (Fig 4A and 4B). Response rates for daily sleep diary entries did not differ between the active (97%) and sham (86%) conditions (*p*>0.05). Similarly, the number of days participants provided usable actigraphy data did not differ between the active (91%) and sham (89%) conditions (*p*>0.05). Protocol acceptability specific to the intervention examined overall fidelity adherence, which has averaged 83–93% across study arms. No differences were detected in the rates of participants meeting threshold for fidelity adherence across study arms when referencing either self-report or the objective assessment (*p*>0.05). Noting that there was not an objective assessment of device adherence to the sham condition. This protocol’s *a priori* definition of “fully adherent” was that participants engage with the device on at least 70% of the intervention period (5 out of every 7 days; therefore, a minimum total of 20 out of 28 days). Accordingly, device adherence has on average exceeded expectations with most adherent participants reporting device use for >23/28 days (Fig 5A and 5B).

**Fig 4 pone.0305305.g004:**
[figure not shown]
Baseline adherence. Sleep diary and actigraphy data collected at baseline (over 14 days) in the active (**A**) and sham (**B**) conditions. The dashed line indicates the 70% threshold for adherence (10 days). Each data point represents a single participant and corresponds to the number of days they have complete data.

**Fig 5 pone.0305305.g005:**
[figure not shown]
Intervention adherence. Device use (self-report and objective), sleep diary and actigraphy data collected during intervention (over 28 days) in the active (**A**) and sham (**B**) conditions. The dashed line indicates the 70% threshold for adherence (20 days). Each data point represents a single participant and corresponds to the number of days they have complete data.

With respect to our primary outcome (ISI score), >95% of participants in both study arms have provided both pre- and post-intervention data. Supplemental sleep related outcomes included wrist-based actigraphy and sleep diary entries, the completeness for both of which was expressed in terms of the number of days with full/usable data (i.e., out of a maximum of 14 days for the baseline period and out of a maximum of 28 days for the intervention period). For both actigraphy and sleep diaries, we reported >83% of participants have complete data, defined as a minimum of 10 days of data recorded at baseline (Fig 4A and 4B) and 20 days of data recorded during the intervention period (Fig 5A and 5B), reflecting >70% of days for both periods.

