## Materials and methods

### Overview and ethics

LION is a sham-controlled, participant-masked, randomized controlled trial (NCT03968874), investigating primarily, the efficacy of morning bright light therapy (MBLT) to improve sleep quality, cognitive function, and quality of life in Veterans with mTBI, and secondarily, the feasibility and acceptability of implementing a fully remote clinical trial within the VA. Participants were randomized and allocated 2:1 to active (MBLT) or sham (negative ion generator) study arms, with a target total sample size of n = 120 participants with complete pre- and post-intervention data (~80% of the data has been collected so far). Primary outcomes were changes between groups from baseline to post-intervention (28 days), and baseline to follow-up (56 days). All participants that expressed interest, screened eligible, and were enrolled in the study were processed according to the Standard Protocol Items and Recommendations for Interventional Trials (SPIRIT) guidelines (Fig 1). This project is sponsored by the Military Traumatic Brain Injury Initiative (MTBI^2^) and approved by a joint Institutional Review Board (IRB) at the VA Portland Health Care System (VAPORHCS; #4268 and #4002) and Oregon Health & Science University (OHSU; #19411), as well as the Department of Defense Office of Human Research Oversight (OHRO). All participants provided, or will provide, verbal and written informed consent prior to participation.

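### The text reports pre- and post-intervention ISI for more than 95% of both arms; Table 3 shows 87% and 89%, yet all 104 count as complete towards the 120

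*Protocol article*

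**What the plan says.** All references are to the protocol article.

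- **Primary outcome and sample size.** The Outcomes section makes the ISI primary. The power paragraph below Fig 1 bases the total of 120 on the ISI.
- **Target.** Overview and ethics sets a "target total sample size of n = 120 participants with complete pre- and post-intervention data".
- **Completeness in the text.** The Results paragraph after Fig 5 says: "With respect to our primary outcome (ISI score), >95% of participants in both study arms have provided both pre- and post-intervention data".
- **Completeness in the table.** In Table 3, under the primary sleep outcome, the row block "Insomnia severity index" gives pre-intervention counts of 47, 22, 24 and 11, and post-intervention counts of 43, 17, 21 and 10. The columns are MBLT mTBI, MBLT no TBI, sham mTBI and sham no TBI.
- **Accrual count.** The retention paragraph in Results says that "complete pre- and post-intervention data has been recorded in n = 104 participants". The Discussion sets those 104 against the 120 and describes them as about 80% of it.
- **Missing data.** Statistical analyses ties the method to the missing rate. The first tier reads: "1) <5% without evidence of differential patterns of missingness we will consider this negligible". From 5% to 25%, multiple imputation applies.
- **Other completeness statements.** The abstract puts missing data below 15% of key outcome variables. The Discussion puts complete data in key outcome measures above 90% of the 104.

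**The concern.** One quantity, the share of participants with both ISI scores, appears with two incompatible values, and it concerns the primary endpoint. The article also names completeness of the primary outcomes as one of its acceptability measures, so a headline feasibility result is affected.

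The same discrepancy reaches the accrual count. The 120 was sized on the ISI and defined by complete pre/post data, so a participant without a post-intervention ISI does not meet the definition. If the table is right, the reported 104 overstates progress on the quantity that the sample size was calculated for. Even if the text were right, a rate above 95% would not by itself make all 104 complete on the ISI.

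The two values also fall on opposite sides of the 5% boundary in the missing-data rule.

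**Working it through.** **Inputs.** ISI counts from Table 3; target of 120 from Overview and ethics; 104 reported complete from Results and Discussion; missing-data tiers from Statistical analyses.

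**Step 1. Try to reproduce the stated figure.** Share = post-intervention count / pre-intervention count. The pre-intervention count is 100% in every column, so this is the largest share that can have both scores.

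| Group | Pre | Post | Share |
|---|---|---|---|
| MBLT, mTBI | 47 | 43 | 91.5% |
| MBLT, no TBI | 22 | 17 | 77.3% |
| Sham, mTBI | 24 | 21 | 87.5% |
| Sham, no TBI | 11 | 10 | 90.9% |
| MBLT, all | 69 | 60 | 87.0% |
| Sham, all | 35 | 31 | 88.6% |
| mTBI, both arms | 71 | 64 | 90.1% |
| No TBI, both arms | 33 | 27 | 81.8% |
| All | 104 | 91 | 87.5% |

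The stated figure is not reproduced. To exceed 95%, MBLT would need at least 66 of 69 (0.95 × 69 = 65.55) and sham at least 34 of 35 (0.95 × 35 = 33.25). The percentages printed in the table (91, 77, 88, 91) agree with its counts, so a broken extraction is not the explanation.

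**Step 2. Look for a reading that rescues it.**
- The post-intervention full questionnaire battery row has 43, 17, 20 and 11. Taking the higher of the two rows in each column gives 43 + 17 + 21 + 11 = 92, and 92/104 = 88.5%.
- The Discussion gives the sham no-TBI group as 10 rather than 11. With that denominator, sham is 31/(24 + 10) = 91.2%.
- The post-intervention cognitive assessment does exceed 95% in both arms: 67/69 = 97.1% and 34/35 = 97.1%. That the text took its figure from this row is only a possibility.

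**Step 3. Accrual.**
- Without a post-intervention ISI: 104 − 91 = 13 (MBLT 69 − 60 = 9; sham 35 − 31 = 4).
- Progress as reported: 104/120 = 86.7%. Progress by ISI: 91/120 = 75.8%. The stated figure of about 80% is neither.
- Counting on to 120 in the same way leaves 16 to add. At 87.5% this gives 91 + 14 = 105 with both scores. If all 16 supplied both, the total would be 107.
- For 120 with both scores at the same rate: 120/0.875 = 137.1, so 138 counted participants.

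**Step 4. Missing-data tier.** 13/104 = 12.5% (MBLT 13.0%, sham 11.4%). This lies between 5% and 25%. A rate above 95% complete would lie below 5%.

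**Step 5. The other statements.** A 12.5% missing rate fits the abstract's figure of under 15%. It does not fit the Discussion's figure of more than 90% complete, if the ISI is among the key measures.

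**The case against.** The strongest reply is that this is an interim feasibility sentence with no bearing on the efficacy analysis. The missing-data rule is written for the future, so the tier will follow the missingness found in the final data and not a sentence in the Results. The mixed models accommodate data missing at random in any case. The table could also be the faulty source. The Discussion's sham no-TBI figures (10 participants, 60% biospecimens) differ from Table 3 (11 participants, 55%), which suggests that text and table may come from different data cuts. In that same column, the battery is listed as 11 of 11 but the ISI as 10 of 11.

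Much of this stands. The sentence does not choose the tier; it only implies a different one from the table. The documents do not settle which source is wrong. What does not fall away is that the two figures cannot both be right, and that counting all 104 as complete conflicts with the table.

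Three stronger readings are tempting and are not supported:
- **That enrolment is being closed on a wrong count.** Recruitment is described as ongoing, and no passage says how completeness will be judged when accrual stops.
- **That the trial is underpowered.** With the stated SDs of 12% and 7.3%, power for a 7% difference at 70/35 is 95.6% (Welch) or 88.0% (pooled), still above 85%. It falls to about 80% only with an SD of 12% in both arms, which the article does not state.
- **That missingness is differential.** Within MBLT the contrast is 5/22 against 4/47 (Fisher p about 0.13). Between arms it is 9/69 against 4/35 (p = 1.0).

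**Conclusion.** The contradiction is exact and needs no outside assumption: more than 95% in both arms in the text, against 87.0% and 88.6% in Table 3. The count of 104 complete participants conflicts with the same table.

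What follows is conditional on the table being right. In that case 13 of the 104 lack the primary outcome, progress is 91 of 120 (76%), and the missing rate among those counted is 12.5%. The figure of about 105 at a count of 120 is an extrapolation that assumes the current rate continues and that completeness goes on being counted as it was for the 104.

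The 12.5% describes only the 104 counted as complete. The rate for the intention-to-treat set will also reflect any withdrawals after randomisation. The point concerns the primary endpoint and the accrual count, so it is more than a clerical slip. It does not show harm to power or bias in the treatment comparison.

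**What to change.** 1. Query the database for ISI presence at both times, by arm and TBI status.
2. Reconcile the ISI rows of Table 3, the over-95% sentence and the count of 104 in Results, and the roughly 80% and over-90% statements in the Discussion. State the data cut for each.
3. Count a participant towards the 120 only if the ISI is present both pre- and post-intervention.
4. If the table is right, restate completeness as 87% (MBLT) and 89% (sham) and progress as 91 of 120 (76%). Note that 12.5% missing falls in the 5–25% tier. If the missing ISI forms exist, correct the table instead.

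The cost of reconciling is a database query and corrected figures, with a less favourable completeness rate if the table stands. Step 3 then has a further cost: holding to 120 with the ISI would take about 138 participants by the present count, 18 more than counting to 120. If the sponsor does not extend accrual, no further participants are needed, but the expected number with the ISI, about 105, should then be stated openly.
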